#### Data analysis

The IBM-SPBB version 20 will be used to perform a statistical analysis. Descriptive statistics (frequency, %), mean (standard deviation)) will be used to describe the demographic data of the participants.

To determine the dose-response relationship of this intervention program on pain, a generalized estimating equation with quadratic and higher order terms will be used. To examine the intervention effect, a t-test will be used to compare the mean pain intensity, functional mobility, physical activity, loneliness and happiness levels, and use of non-pharmacological methods collected at four time points, that is, between P0 and P1, P1 and P2, P1 and P3 (for pain only), and between P0 and P2, P0 and P3, and P2 and P3 (for other variables). The Kolmogorov-Smirnov normality test will be used to examine the normality of the outcome variables. If the data do not follow a normal distribution, we will use the Wilcoxon Signed-rank test and the Mann-Whitney U test for within-group and between-group comparisons, respectively. A *P* value of <0.05 will be considered statistically significant. An intention-to-treat analysis will be conducted for any missing data. All data from the ‘I can do it’ booklet will be gathered and used to calculate the participation rate.

The questionnaires for the volunteers will be compared using the McNemar test and a pair sample t-test for quantitative data. Qualitative data will be analyzed using content analysis [31]. Sentences or parts of sentences will be identified as meaningful units in each questionnaire. The meaningful units will be categorized into themes related to the perception of program. The themes will be compared and discussed to establish the credibility of the interpretations.

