Our research team conducted a search of databases (PubMed and ScienceDirect) to study the application of PVs in intervention programs for older adults in Hong Kong from 1998 to the present. Four studies were identified, and they have been shown to achieve positive outcomes. However, the programs studied were those for healthy living, coping with stress, post-discharge support, and physical activity [15-18]. No pain management programs involving PVs were found. PVs were chosen over other forms of social support as the Hong Kong population is aging and people are living longer. After retirement, some older adults are still enthusiastic about serving the community. Therefore, we will select the PVs from the Institute of Active Ageing (IAA), which is dedicated to promoting active aging and the view of older adults as important contributors to society. As the IPMP has already been validated and published, and its effectiveness has been established, the effectiveness of the IPMP among older adults is well understood; however, whether this effect will be extended with the use of PVs is unknown. Therefore, in the present study we will attempt to test only the effectiveness of an IPMP that will be sustained by PVs.

The aim of this study is to determine the feasibility of PVs in an IPMP for Hong Kong older adults with chronic pain. According to the literature, pain management programs range from 4 weeks to 8 weeks. As the previous 8-week IPMP has already been validated, in this study we would also like to examine the dose-response relationship of an IPMP with PVs (that is, the possibly nonlinear association between intervention duration and pain intensity score). Our objective is to run a pilot study for a future main study with a randomized controlled design. It is hypothesized that the implementation of an IPMP supplemented with PVs for older adults with chronic pain will lead to improvements in levels of pain intensity, functional mobility, physical activity, loneliness, and happiness, and in the use of non-pharmacological pain-relieving methods.

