## Method/Design

### Design

It will be a single group trial.

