### Samples

#### Participants

The participants will be recruited from one nursing home in Hong Kong. The home-in-charge nurse will be approached and invited to participate in the study. Older adults in the nursing home who are interested to participate will be recruited according to the inclusion criteria. The present study will be a pilot study with 30 participants. Inclusion criteria are older adults aged ≥60, who scored ≥6 in the Abbreviated Mental Test [19], have been experiencing non-malignant physical pain or discomfort either all the time or on and off for more than three months, scored ≥1 in the frailty index [20], and are able to speak and understand Cantonese. Exclusion criteria are those with cognitive impairment and a history of mental disorders, and those with cancer and currently on cancer treatment, since the present study is for older adults with non-malignant pain. As this program involves physical activities, those suffering from conditions that limit safe participation will be excluded. Examples include those who have had a fracture or undergone surgery in the past two months, those with severe chronic obstructive pulmonary disease, acute stroke, and acute myocardial infarction. The ratio of participants to PVs is 1:1. PVs who have not been paired with participants will be responsible for making overall observations during the sessions. Participants and PVs will also be matched according to gender and dialect. Since it is essential that actions be repeated in response to stable cues to become a habit, the participants will be accompanied by the same PV during the study [21].

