### Study design

#### Procedure

As in Figure 1, the following data will be collected on the participants at P0 (baseline, that is, before the IPMP): demographic data (age, gender, marital status, medical history, educational level), pain score, functional mobility, physical activity, loneliness level, happiness level, and use of non-pharmacological pain management methods. An 8-week group-based IPMP during weeks 1 to 8 will then be offered. Each session will involve a group of 15 participants. To detect the dose-response relationship, pain scores will be collected at the beginning of each session from weeks 1 to 8 (P1). At week 8 (P2) and week 12 (P3), the following data will be collected: pain score, functional mobility, physical activity, loneliness level, happiness level, and use of non-pharmacological methods to relieve pain.As in Figure 2, PVs will complete the questionnaire for volunteers at four time points, that is, before the training (V0), after the training (V1), at week 4 (V2), and at week 12 (V3).

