#### Preparation of the booklet and relevant materials

The booklet and other relevant materials will be prepared as indicated below:

1. ‘I can do it’ booklet. A booklet will be given to each participant at the beginning of the IPMP, and they will be asked to bring this booklet to all sessions. The booklet summarizes the key points of pain management strategies learned in the program and demonstrates the steps of various types of exercises. This booklet of each participant will be stamped every time they participate in a session. Outside the classroom, the booklet will also be used to record their participation in exercises or their application of other non-pharmacological methods. The booklet will be validated by the research team.

2. Materials for the IPMP. Various class materials will be delivered in the IPMP. Materials include music CDs for participants to listen to when they practice deep breathing; herbal tea to stimulate their taste buds; and scissors, glue, origami paper, and colorful art materials for the arts and crafts therapy to facilitate fine motor activities. All of the materials will be kept in the nursing home for the PVs to use until the end of the study.

3. Guidebook for peer volunteers. A guidebook will be developed for the PVs to ensure that the procedure and content of each session are standardized. Safety and privacy issues will also be mentioned in the guidebook. Links to webpages on pain management strategies will be printed for their reference. The guidebook will also include guidelines on how to use the ‘I can do it’ booklet. The guidebook will be validated by the research team, as well as by an advanced practice nurse, consultant, and physiotherapist from the Pain Clinic.

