#### Evidence-based practice: Integrated pain management program (IPMP)

The participants will be given an 8-week group-based IPMP supplemented with PVs. Table 1 shows the details of the IPMP. We will follow the study design of a previous study [7]. There will be 16 sessions, with two 1-hour sessions each week.

**Table 1 T1:** Integrated pain management program (IPMP)

**Week**	**Session 1**			**Session 2**		
	**(research assistant and peer volunteers)**			**(peer volunteers only)**		
	Interactive teaching and sharing	Exercise	Entry	Revision	Exercise	Entry
		(20 minutes)	(10 minutes)	(30 minutes)	(20 minutes)	(10 minutes)
	(30 minutes)					
1	Introduction on pain	Deep breathing	Research assistant and PVs will work together with the participants to make entries in the ‘I can do it’ booklet on the activity of the day.	PVs will use the ‘I can do it’ booklet to review the content taught in the previous session and continue any remaining arts and crafts activities.	Deep breathing	PVs will work together with the participants to make entries into the ‘I can do it’ booklet on the activity of the day.
	Impact of pain					
	Drug therapy					
2	Hot pad and cold pad	Relaxation exercise			Relaxation exercise	
3	Music therapy	Warm-up exercise			Warm-up exercise	
4	Massage	Shoulder and neck exercise			Shoulder and neck exercise	
5	Use of five sensations as nondrug therapies: making a photo album	Lower arm exercise			Lower arm exercise	
6	Use of five sensations as nondrug therapies: making a bag of dried flowers	Towel dancing			Towel dancing	
7	Use of five sensations as nondrug therapies: tasting of tea	Towel dancing			Towel dancing	
8	Wrapped up	Whole body exercise			Whole body exercise	

Session 1 of each week aims to empower the older adults with knowledge of how to manage pain and to demonstrate the procedure of the selected exercise. The research assistant (RA) will lead the sessions and the PVs will help the RA to guide the participants in doing exercises and assist them in carrying out the activities. Session 1 includes:

1. 30 minutes of interactive teaching and sharing. The contents include an introduction on pain, the impact of pain, drug therapy, five sensation therapy (touch, smell, taste, hearing, and vision), making a photo album and bags of dried flowers, and a tea tasting.

2. 20 minutes of exercise. Specific exercises for the shoulder, neck, arms, and the whole body, and balancing and towel dancing will be taught.

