## Discussion

The 8-week group-based IPMP has already been validated and published, and its effectiveness has been established. Interventions that include some type of social support have great potential to increase participation and adherence, raising the question of whether the effects of an IPMP can be extended with the use of PVs. This study is aimed at evaluating the feasibility of using PVs in an IPMP for Hong Kong older adults with chronic pain.

This pilot study helps older adults to control their pain by providing a PV to encourage and accompany them. The limitations of this study should be noted. As it is only a pilot study lasting 12 weeks, long-term changes in the outcome measures cannot be evaluated. Moreover, there may be a ‘learning effect’, which will familiarize the participants with measuring instrument in the study as there will be a repeated measure of pain intensity in the beginning of all 16 training sessions. This study provides evidence for future, larger studies that utilize a randomized controlled design and a possibly longer follow-up time to adjust this ‘learning effect’ and to investigate whether PVs should be integrated in programs for older adults with chronic pain. This will help to promote health among older adults in the long term.

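### The planned dose-response analysis can only describe pain over time, because all 30 residents follow one uncontrolled schedule in which dose and elapsed time are the same variable

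*Protocol article*

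**What the plan says.** The Background adds a dose-response aim to the feasibility aim and explains it as "the possibly nonlinear association between intervention duration and pain intensity score". It does so just after noting that published programmes last between 4 and 8 weeks. The Procedure section has pain rated at the start of every session in weeks 1 to 8 for this purpose. The Data analysis section then commits to the model: "To determine the dose-response relationship of this intervention program on pain, a generalized estimating equation with quadratic and higher order terms will be used".

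The design is given in separate places:
- Design: "It will be a single group trial".
- Participants: "The present study will be a pilot study with 30 participants".
- Integrated pain management program: "There will be 16 sessions, with two 1-hour sessions each week". Table 1 gives each week its own topic, and the exercise also changes in most weeks.
- Procedure: "Each session will involve a group of 15 participants".

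Attendance is recorded: "This booklet of each participant will be stamped every time they participate in a session". The Data analysis section uses the booklet data for a participation rate. The Discussion concedes a learning effect on the measuring instrument, "as there will be a repeated measure of pain intensity in the beginning of all 16 training sessions", and leaves its adjustment to later, larger studies.

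**The concern.** A dose-response relationship of a programme on pain says what more or less of the programme does to pain. To estimate it, some residents must receive a different amount from others at the same point in time, or there must be a comparator that shows what time alone does. This design has neither. At each reading every resident has been scheduled for the same number of sessions, over the same number of weeks, covering the same topics.

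What is at stake is the meaning of the result. A falling or flattening curve would be reported as the programme's dose-response, although the same curve could arise from the natural course of pain that comes and goes (which the inclusion criteria allow) or from growing familiarity with the scale. The study is a pilot for a randomised trial, so a mislabelled curve could be carried forward as evidence about dose.

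**Working it through.** The protocol gives no error rate, power or sample-size calculation for this analysis, so there is no figure to reproduce.

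**1. Can dose be separated from time?**
- Inputs from the protocol: one group, 30 residents, 16 sessions, two per week, one pain rating at the start of each session.
- At the rating before session k (k = 1 to 16), the sessions already scheduled number k − 1 and the weeks elapsed are about (k − 1)/2, for every resident.
- Hence sessions scheduled = 2 × weeks elapsed. The design matrix with columns [intercept, sessions scheduled, weeks elapsed] has rank 2 out of 3.
- Unequal gaps between the two sessions of a week would not help. Dose would still be a fixed function of time shared by all, so any polynomial in dose is also a curve in time.
- Content is tied to the same index. In Table 1, week 4 is massage with shoulder and neck exercise, and week 8 is the closing session with whole-body exercise.

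**2. How often would pure drift be labelled dose-response?**
- Assumptions, because the protocol gives no variability: mean pain 5, SD 2, ratings rounded to 0–10, and correlation between two readings of one resident 0.4 + 0.4 × 0.7^lag. The true programme effect is zero. Pain drifts down by d points in total over the 16 readings, quickly at first and then levelling off.
- Test: joint linear and quadratic terms, with an F reference that holds its 5% size. 3,000 simulated trials per row.

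| Drift d (points) | Declared significant |
|---|---|
| 0.25 | 7.6% |
| 0.5 | 19.2% |
| 1.0 | 61.1% |

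The test works correctly here, since there is a trend. Only the label is wrong.

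**3. Secondary: size of the trend test with 30 clusters.** This applies only if an uncorrected robust variance and a chi-square reference are used, which the protocol does not say. For complete, normally distributed data and q polynomial terms, the robust joint Wald statistic W is distributed as [Nq/(N − q)] × F(q, N − q). Its true size at nominal 5% is P[F(q, N − q) > c(N − q)/(Nq)], where c is the 95% chi-square point on q degrees of freedom. With N = 30:
- q = 1: 3.841 × 29/30 = 3.713, size 6.4%.
- q = 2: 5.991 × 28/60 = 2.796, size 7.8%.
- q = 3: 7.815 × 27/90 = 2.345, size 9.5%.

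Simulation with flat pain agrees: 7.3–8.3% for the quadratic joint test and 8.6–10.1% for the cubic, across several correlation structures. The quadratic term tested alone rejects in 5.7–6.5%. A joint F-type reference with the order fixed returns the size to about 5% (4.3–5.6% for degrees 1 to 5).

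**The case against.** The strongest reply is that the Background speaks of an association, that this is an added aim of a feasibility pilot, that the intervention effect is examined separately by t-tests, and that the learning effect is disclosed. Part of this stands. The model can validly describe the mean pain trajectory, and the pilot status lowers the stakes. But the Data analysis section claims a dose-response relationship of the programme on pain, which is more than association. The disclosed limitation names the rating effect only, not the complete overlap of dose with time.

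It can also be said that the protocol does not state whether the model's regressor is scheduled or attended sessions. That is fair: the rank result applies to scheduled dose, and it would be an inference from silence to say that attendance is ignored. Attended sessions may differ between residents, but they are self-selected, so using them would not restore a causal reading.

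A reader might infer four stronger points that the document does not support:
- *That the model will reject too often.* Polynomial order, working correlation and variance correction are commonly left to an analysis plan, and none is shown here.
- *That nonlinearity will be seriously over-called.* The 7.8% and 9.5% are joint tests that include the linear term. A single-term test of curvature exceeds 5% by only 1 to 2 points.
- *That the curve will set the number of weeks.* No such decision rule is stated. The 4- to 8-week range is background.
- *That alternating session types distort the readings.* Pain is rated before each session's content, and nothing says that the rating differs by session type.

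Regression to the mean is also a weaker argument here than usual, because eligibility sets no minimum pain score.

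**Conclusion.** The point holds for identifiability. With one schedule and no comparator, scheduled dose and elapsed time are perfectly collinear. The analysis as written gives a time course and supports no statement about the effect of dose. This follows from the design alone, rests on no assumed figure, and cannot be cured by an analysis plan.

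The 19% and 61% illustrate the consequence and depend on the assumed SD, correlation and shape of drift. The error-rate figures are secondary and hold only for an uncorrected robust test with a chi-square reference. The matter concerns an added aim rather than the main comparisons, but it changes what the trial may conclude, so it should be corrected.

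**What to change.** In the Background, Procedure and Data analysis sections, reword the aim and the analysis as the *time course of pain during the programme*. State that no conclusion about the effect of dose, or about the duration required, will be drawn from it.

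Add one exploratory model with cumulative sessions attended, taken from the stamps, alongside session number, and label it observational. It will be informative only as far as attendance varies between residents, and pain may itself influence attendance.

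If no analysis plan already does so, fix the polynomial order in advance and refer the joint test to a small-sample F-type distribution.

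The cost is a weaker stated aim, one extra model from data already collected, and slightly fewer significant trend tests. Estimating dose-response itself would need a concurrent control or durations that differ between residents, preferably by randomisation. That belongs to the later trial.

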### Outcome assessment

#### Primary outcome

The primary outcome measure is pain intensity, which will be assessed using an 11-point numeric rating scale (NRS). The NRS is a line marked in equal segments from 0 (no pain) to 10 (worst possible pain). The NRS has been shown to be a reliable and valid measure of pain intensity and pain distress in older patients with persistent pain [23].

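### The listed t-tests never compare the primary outcome, pain, between baseline and week 8 or week 12; every pain test uses P1, which is 16 session readings with no stated summary

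*Protocol article*

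**What the plan says.** The Primary outcome section states: "The primary outcome measure is pain intensity, which will be assessed using an 11-point numeric rating scale (NRS").

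The Procedure section sets the pain schedule.

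- Baseline: "the following data will be collected on the participants at P0 (baseline, that is, before the IPMP"), and pain score is in the list that follows.
- During the programme: "pain scores will be collected at the beginning of each session from weeks 1 to 8 (P1").
- Afterwards: "At week 8 (P2) and week 12 (P3), the following data will be collected: pain score, functional mobility" and the remaining outcomes.

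The section describing the IPMP says "There will be 16 sessions, with two 1-hour sessions each week", and the Discussion confirms that "there will be a repeated measure of pain intensity in the beginning of all 16 training sessions".

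The Data analysis section gives t-tests (Wilcoxon if the data are not normal) as the means of examining the intervention effect. It refers to four time points and lists the pairs as "between P0 and P1, P1 and P2, P1 and P3 (for pain only), and between P0 and P2, P0 and P3", followed by P2 with P3. The first three pairs are marked as being for pain only and the last three as being for the other variables. Separately, a generalized estimating equation (GEE) with quadratic and higher-order terms is planned for the dose-response relationship on pain.

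**The concern.** The protocol hypothesises that pain will improve, and it is concerned with whether the benefit is sustained; the volunteers keep visiting in weeks 9 to 12. Three contrasts answer those questions directly: baseline to week 8 (P0-P2), baseline to week 12 (P0-P3) and week 8 to week 12 (P2-P3). The list gives all three to the other participant outcomes and none to the primary one.

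The three tests that pain does receive all depend on P1. The analysis section treats P1 as a single occasion, but the schedule makes it a series running through the whole programme. The first reading precedes any programme content, and the last two fall in week 8, the same week as P2. Until someone decides how P1 enters a paired test, none of the listed pain tests is defined. Most of the possible choices compare part-treated residents with baseline or with the end of the programme, which is not the programme effect.

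**Working it through.** The protocol states no power, effect size or SD for pain, so there is no figure of its own to reproduce.

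**1. Which pairs pain receives.** Four labels give 4 × 3 / 2 = 6 pairs.

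| Pair | What it measures | Listed for |
|---|---|---|
| P0-P1 | baseline to in-programme | pain |
| P1-P2 | in-programme to week 8 | pain |
| P1-P3 | in-programme to week 12 | pain |
| P0-P2 | baseline to week 8 | other variables |
| P0-P3 | baseline to week 12 | other variables |
| P2-P3 | week 8 to week 12 | other variables |

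The lists split three and three with no overlap. Every pain pair contains P1, and every pair without P1 is withheld from pain.

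**2. What P1 is.** 8 weeks × 2 sessions = 16 readings per participant, matching the count in the Discussion.

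**3. How much of the change P0-P1 captures.** Assume that pain falls linearly over the 16 sessions, so that the reading before session k reflects (k − 1)/16 of the total change.

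- P1 = first reading: 0/16 = 0%.
- P1 = mean of 16: (0 + 1 + … + 15)/(16 × 16) = 120/256 = 46.9%, leaving 53.1% for P1-P2.
- P1 = last reading: 15/16 = 93.8%.

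**4. Illustrative power with P1 as the mean of 16.** From the protocol: n = 30 and significance level 0.05. Assumed: two-sided test, true fall of 1.0 NRS point, within-person SD (SDw) of 1.3 or 1.6, independent within-person errors. Paired-t power comes from the noncentral t with 29 degrees of freedom and noncentrality change × √30 / SD of the difference.

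- SD of the P0-P2 difference: SDw × √2 = 1.838 (SDw 1.3) or 2.263 (SDw 1.6).
- SD of the P0-P1 or P1-P2 difference: SDw × √(1 + 1/16) = 1.340 or 1.649.
- Example, SDw 1.3: the noncentrality is 1.0 × 5.477/1.838 = 2.98 for P0-P2, and 0.469 × 5.477/1.340 = 1.92 for P0-P1 under a linear fall.

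If the fall is complete after 8 sessions (week 4), the mean of 16 readings carries 71.9% of it; if after 4 sessions (week 2), 84.4%.

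| Shape of fall | P0-P1 (SDw 1.3 / 1.6) | P1-P2 (SDw 1.3 / 1.6) | P0-P2 (SDw 1.3 / 1.6) |
|---|---|---|---|
| Linear | 46% / 32% | 56% / 40% | 82% / 65% |
| Complete by week 4 | 81% / 64% | 20% / 15% | 82% / 65% |
| Complete by week 2 | 92% / 77% | 9% / 8% | 82% / 65% |

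**The case against.** **It may be a drafting slip.** The P1 pairs may be marked for pain only because pain alone is collected at P1, with the remaining pairs meant for all outcomes. That is plausible. But the label on the second group excludes pain as written, and P1 would still be undefined in three planned tests.

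**The GEE covers pain over time.** It does model pain, so it is not true that pain is analysed only through the t-tests. But its stated purpose is dose-response, the Procedure section ties that to the session readings, and no contrast of baseline with week 8 or week 12 is named. This softens the point without curing it.

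**P1 could be the first reading.** If so, P1-P2 and P1-P3 come close to baseline against end of programme and against follow-up. The protocol does not say this.

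**The change can still be recovered.** With complete data and one fixed definition of P1, the mean P0-P1 and P1-P2 changes add up to the P0-P2 change. That is right: the data exist, and what is missing is a named comparison.

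**Stronger readings are tempting.** A reader might infer from the low P1-P2 figures that a fast-acting programme would be judged to have no effect. The document does not support that, because P0-P1 is also a planned pain test and in the rapid-fall scenarios it detects the effect about as well as P0-P2, or better. A reader might also add a family-wise error rate over the listed tests. Figures of that kind assume independent tests, whereas the three pain tests share P1, and ranking of contrasts is commonly left to an analysis plan that is not shown. The point does not need it.

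**It is a single-group pilot with a feasibility aim.** True, but the protocol also hypothesises improvement in pain and will use the results to judge the need for a larger randomized study.

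**Conclusion.** The point holds on the text. For its primary outcome the protocol lists three t-tests, all resting on an undefined P1, and it omits the three contrasts that it gives to every other participant outcome. This is not a detail left to another document: the article states the pairs explicitly, and the list does not fit the primary outcome.

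The size depends on a choice the protocol does not make. Under a linear fall, P0-P1 carries anything from 0% to 94% of the programme change. If P1 is the mean, a linear fall leaves power at 46% to 32% (P0-P1) and 56% to 40% (P1-P2), against 82% to 65% for P0-P2. If the fall is rapid, detection through P0-P1 is not materially worse, but that test would still estimate 72% or 84% of the change rather than all of it. The 1.0-point fall, the SDs, the shapes and the independent errors are all assumptions; the mismatch in the list of pairs depends on none of them.

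**What to change.** In the Data analysis section:

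1. List P0-P2, P0-P3 and P2-P3 for pain, as for the other outcomes.
2. Name the P0-P2 change in NRS as the primary pain contrast.
3. Remove P1 from the t-test list and state that the 16 session readings are used only in the GEE.

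Averaging P0 with the reading before the first session, as a second baseline, is optional and not needed to correct the error.

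The cost is a change of wording. Pain is already collected at P0, P2 and P3, so no visit, instrument or participant is added. The Trial status section reports that recruitment was still under way, so at that stage the change could be made before any analysis.

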Another 8-week integrated pain management program (IPMP) was carried out among Hong Kong nursing home residents [7]. A total of 535 older adults were randomized into an experimental group (n = 296) and a control group (n = 239). The participants in the control group only received regular care but not the IPMP. The participants in the experimental group received the IPMP, which included a 30-minute physical exercise program (PEP) and 30 minutes of either multisensory stimulation therapy or an arts and crafts activity each week. The PEP included exercises in muscle strengthening, stretching, and balancing, and was conducted in small groups of 10 to 15 older residents. In the multisensory session, relaxation techniques to control pain and the use of the five primary senses were taught. In the arts and crafts session, older adults made artwork such as photo albums, paper flowers, and paper fans to exercise their fine motor activities and for multisensory stimulation. Upon completing the program, the participants in the experimental group showed a significantly higher reduction in pain scores, higher happiness and life satisfaction scores, and lower scores in loneliness and depression than were observed among the control group; no significant differences were seen in the control group. A significant increase in the use of non-pharmacological methods of pain relief was also seen among the participants in the experimental group as compared to the control group.

Although the pain management program, which includes physical activity, has been shown to have health benefits and improve pain management among older adults [8], studies have found educational interventions to be effective among older adults only over the short term [9]. People who participated in these interventional programs often fell back into their old habits of inactivity after completing the program [10]. Therefore, it is important to develop interventions that can be sustained over time.

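### With 30 residents, a non-significant week-8 to week-12 test does not show that gains were kept, and pain has no such contrast listed

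*Protocol article*

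**What the plan says.** The Background section gives durability as a reason for the study: earlier programmes worked only in the short term, so "it is important to develop interventions that can be sustained over time". It says that whether volunteers extend the programme's effect is unknown, and concludes that "in the present study we will attempt to test only the effectiveness of an IPMP that will be sustained by PVs". The Discussion raises the same question of extension.

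The design is fixed in two short statements: "It will be a single group trial" and "The present study will be a pilot study with 30 participants". Under Procedure, P2 is week 8 and P3 is week 12. P1 is the series of pain scores taken at the start of each session in weeks 1 to 8. Under Roles of peer volunteers, the volunteers go on visiting weekly in weeks 9 to 12.

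Data analysis introduces the tests with "To examine the intervention effect, a t-test will be used to compare the mean pain intensity" and continues to the other outcomes. The contrasts for pain are "between P0 and P1, P1 and P2, P1 and P3 (for pain only". For everything else they are "and between P0 and P2, P0 and P3, and P2 and P3 (for other variables". The only criterion is that a P "value of <0.05 will be considered statistically significant". No margin for an acceptable loss is given.

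**The concern.** The weeks after the taught programme ends are the only window in which the trial can look at whether gains last. For mobility, physical activity, loneliness, happiness and use of non-drug methods, the analysis of that window is a test for change. If it is non-significant, the data may be compatible with full retention or with a sizeable loss. The test alone does not separate the two, and the smaller the completed sample, the more often it will be non-significant.

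For pain the position is weaker. Neither week 8 against week 12 nor baseline against week 12 is listed. The only pain contrast reaching week 12 is P1-P3, and P1 is a run of up to 16 readings taken during treatment, not the end-of-programme value.

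At stake is what the pilot passes on. The Abstract says that its results will be used to assess the need for a larger randomized study. A statement that gains held to week 12 would be part of that case, and it could rest on low precision.

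**Working it through.** **Inputs.** From the protocol: 30 residents, one group, significance at P<0.05, a t-test of means, P2 at week 8, P3 at week 12. Assumed, because the article does not say: paired test, two-sided, 30 complete pairs (24 as a 20% dropout case). No SD, effect size, power or margin is given, so there is no figure of the plan's own to reproduce. Results are in units of SD_d, the SD of the within-person change.

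**1. Precision.** The 95% CI half-width is t(0.975, n-1)/√n.
- n = 30: 2.045/5.477 = 0.37 SD_d.
- n = 24: 2.069/4.899 = 0.42 SD_d.

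**2. Chance that a true loss is missed.** Power is taken from the noncentral t distribution with n-1 degrees of freedom and noncentrality d√n; the chance of a non-significant result is 1 minus power.

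| True P2-P3 loss (SD_d) | Power, n = 30 | Non-significant, n = 30 | Non-significant, n = 24 |
|---|---|---|---|
| 0.2 | 0.185 | 82% | 84% |
| 0.3 | 0.355 | 65% | 71% |
| 0.4 | 0.563 | 44% | 53% |
| 0.5 | 0.754 | 25% | 35% |
| 0.8 | 0.988 | 1% | 4% |

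Power of 80% needs a change of 0.53 SD_d with 30 pairs and 0.60 with 24.

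**3. What P0-P3 adds.** Take a week-8 gain of 1.0 SD_d and the same SD_d for each pair of time points (an assumption). If 60% of the gain is lost, 0.4 SD_d remains, and P0-P3 is significant 56% of the time. If half is lost, 0.5 SD_d remains, and it is significant 75% of the time. P0-P3 can therefore be positive after a large loss. It answers whether some gain is present at week 12, not whether the week-8 gain was kept.

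**4. What a maintenance reading would need.** To exclude a loss beyond margin m (one-sided 0.025, 80% power, true change 0), n = ((1.960 + 0.842)/m)². The power column is exact t with 30 residents.

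| Margin m (SD_d) | Residents needed | Power with 30 |
|---|---|---|
| 0.2 | 197 | 18% |
| 0.3 | 88 | 36% |
| 0.4 | 50 | 56% |
| 0.5 | 32 | 75% |

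**5. Pain in scale points, for illustration only.** With SD_d = SD·√(2(1-r)), and assuming an SD of 1.5 to 2.5 points and a correlation r of 0.5 to 0.7, SD_d runs from 1.16 to 2.5. The half-width with 30 residents is then 0.43 to 0.93 points on the 0 to 10 scale.

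**6. Pain contrasts as listed.** Pain: P0-P1, P1-P2, P1-P3. Other outcomes: P0-P2, P0-P3, P2-P3. Set side by side, every other outcome has a baseline-to-week-12 and a week-8-to-week-12 contrast; the primary outcome has neither. The dose-response model for pain is described for scores collected in weeks 1 to 8, so it does not evidently fill the gap.

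**The case against.** The protocol calls itself a feasibility pilot. Its hypothesis is improvement, and the difference tests from baseline suit that. The phrase about being sustained by volunteers describes the programme rather than a tested endpoint. The Discussion concedes that long-term change cannot be evaluated, and leaves to later randomized studies whether volunteers should be integrated. All of this stands and limits the seriousness of the point. It does not remove it: the question of extension is put in both the Background and the Discussion, and weeks 8 to 12 are explicitly tested.

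A reader might also infer more than the protocol supports:

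- *That P2-P3 is the only test bearing on durability.* It is not. P0-P3 is planned for the secondary outcomes, and P1-P3 for pain.
- *That no result of P2-P3 could support maintenance.* A significant further improvement would do so where a week-8 gain had been shown, and a CI from the same data could exclude a large loss: with an observed change of 0, it excludes losses above 0.37 SD_d.
- *That the protocol will call a non-significant result maintenance.* It nowhere says so. That reading is foreseeable because no other is set, but it is not a stated rule.
- *That 30 residents is why nothing can be credited to volunteers.* Attribution fails because there is one group, all with volunteers, and visits continue to week 12. A larger sample would not change that.

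**Conclusion.** The point holds in a limited form. With 30 complete pairs, a non-significant P2-P3 test is the likelier result for true losses of 0.2 and 0.3 SD_d, and still occurs 44% of the time at 0.4, so it cannot be read as evidence that gains were kept. P0-P3 helps only in showing that some gain remains. The clearest defect in the text as written is that the primary outcome has no contrast of week 12 with either week 8 or baseline. This is a matter of reporting and wording in a pilot, not a flaw that invalidates it. The figures rest on a paired two-sided t-test, complete pairs and SD_d units; dropout makes them worse, and the signed-rank fallback was not computed.

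**What to change.** Amend Data analysis as follows.

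1. For every outcome, pain included, report the P3-P2 and P3-P0 changes with 95% CIs.
2. State that a non-significant P2-P3 difference will not be reported as maintenance.
3. If a result is to be described as sustained to week 12, require both a shown P0-P2 gain and a P3-P2 CI that excludes a loss larger than a margin the sponsor sets in advance. The half-width of about 0.37 SD_d shows which margins are realistic with 30 residents.
4. Word any such result as within-group change, not as an effect of the volunteers.

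A half-retention contrast, P3 - 0.5·P2 - 0.5·P0 signed so that positive is benefit, may be used only with the P0-P2 gain condition added. Under equal correlations its SD is √(1.5/2) = 0.866 SD_d. If residents worsen by 0.8 SD_d at week 8 and merely return to baseline, the contrast is 0.4/0.866 = 0.46 of its own SD, and its 95% CI lies above 0 about 69% of the time with no net benefit. Half retention is also a debatable threshold that the documents do not support.

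The cost is a few sentences. Pain, like the other outcomes, is already scheduled at P0, P2 and P3, so no new data are needed. The drawback is that maintenance becomes harder to claim: with gains truly unchanged, 30 residents would exclude a loss of 0.3 SD_d only 36% of the time and of 0.5 SD_d 75% of the time.
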